## Abstract

**Background:**

Adhesions develop in over 90% of patients after intra-abdominal surgery. Adhesion barriers are rarely used despite the high morbidity caused by intra-abdominal adhesions. Only one of the currently available adhesion barriers has demonstrated consistent evidence for reducing adhesions in visceral surgery. This agent has limitations through poor handling characteristics because it is sticky on both sides. C-Qur™ Film is a novel thin film adhesion barrier and it is sticky on only one side, resulting in better handling characteristics. The objective of this study is to assess efficacy and safety of C-Qur™ Film to decrease the incidence of adhesions after colorectal surgery.

**Methods/Design:**

This is a prospective, investigator initiated, randomized, double-blinded, multicenter trial. Eligible patients undergoing colorectal resection requiring temporary loop ileostomy or loop/split colostomy by laparotomy or hand assisted laparoscopy will be included in the trial. Before closure, patients are randomized 1:1 to either the treatment arm (C-Qur™ Film) or control arm (no adhesion barrier). Patients will return 8 to 16 weeks post-colorectal resection for take down of their ostomy. During ostomy takedown, adhesions will be evaluated for incidence, extent, and severity. The primary outcome evaluation will be assessment of adhesions to the incision site. It is hypothesized that the use of C-Qur™ Film underneath the primary incision reduces the incidence of adhesion at the incision by 30%. To demonstrate 30% reduction in the incidence of adhesions, a sample size of 84 patients (32 + 10 per group (25% drop out)) is required (two-sided test, α = 0.05, 80% power).

**Discussion:**

Results of this study add to the evidence on the use of anti-adhesive barriers in open and laparoscopic ‘hand-assisted’ colorectal surgery. We chose incidence of adhesions to the incision site as primary outcome measure since clinical outcomes such as small bowel obstruction, secondary infertility and adhesiolysis related complications are considered multifactorial and difficult to interpret. Incidence of adhesions at repeat surgery is believed to be the most valuable surrogate endpoint for clinically relevant adhesion prevention, since small bowel obstruction and adhesiolysis at repeat surgery are not likely to occur when complete adhesion reduction in a patient is accomplished.

**Trial registration:**

ClinicalTrials.gov Identifier NCT01872650, registration date 6 June 2013.

## Background

Postoperative adhesions develop in more than 90% of patients undergoing an intra-abdominal surgical procedure [1]. These adhesions are known to cause small bowel obstruction, secondary infertility and pain [2–4]. At repeat abdominal surgery, intra-abdominal adhesions necessitate adhesiolysis, leading to increased operating times and substantial risk of intra- and postoperative complications [5, 6]. The clinical implications of adhesions carry a significant health and socioeconomic burden [7, 8].

Adhesions are fibrous bands that connect tissue surfaces where anatomical connections do not normally exist. Adhesions are formed after a tissue surface has been injured (abrasion, desiccation, dissection, *etcetera*) and the subsequent process of fibrinolysis is incomplete [9]. At present, there are several products on the market to combat postsurgical adhesion formation. These are broad coverage adhesion barriers, generally consisting of liquids, like icodextrin 4% (Adept™, Baxter, Deerfield, IL, USA) adhesion reduction solution. These materials may limit adhesion formation by minimizing tissue insult during the surgical procedure when used as an intra-operational lavage. At the conclusion of the surgical procedure, instillation of large volumes of liquid acts to separate tissue surfaces by hydroflotation, limiting tissue-tissue contact. Broad coverage adhesion prevention has the distinct advantage of allowing the surgeon to treat many areas of the intraperitoneal space at once. A disadvantage is the lack of control giving adhesion prevention at sites at risk for complications of adhesion prevention such as an anastomosis. In addition, side effects of abdominal distension and vulvar swelling are commonly encountered in the use of liquids [10]. The second group of barriers consists of local coverage adhesion barriers: films, sprays, or gels that are applied directly to adhesiogenic tissue surfaces to act as a physical barrier that blocks tissue-tissue contact. The barrier is generally only effective when it remains at the site of treatment. This requires the barrier to either be sutured or glued in place or to have tissue adherent properties. All local coverage adhesion barriers require the surgeon to anticipate where adhesions are likely to occur and to apply the barrier directly to those sites. These generally include sites where the peritoneum was interrupted during the surgical procedure, such as under a laparotomy incision to minimize adhesions between the incision site and the viscera [11].

Despite the frequent occurrence of adhesions after surgery and the availability of different adhesion barriers, these barriers are rarely used by general surgeons. This discrepancy might be explained by an underestimation of the impact of adhesions [12]. Also, of all the clinically available adhesion barriers, only HA/CMC (hyaluronate/carboxymethylcellulose) barrier film (Seprafilm™, Sanofi, Paris, France) has demonstrated consistent evidence for reducing adhesions in visceral surgery. Seprafilm™ has limitations through poor handling characteristics because it is sticky on both sides. In a large, prospective, randomized controlled multicenter study on the safety of Seprafilm™, significantly more anastomotic leak and leak-associated complications occurred in the Seprafilm™ group due to the wrapping of Seprafilm™ around an anastomosis [13]. A subgroup analysis of control patients and patients without (593 patients) Seprafilm™ wrapped around the anastomosis showed no significant difference. Therefore, wrapping the suture or staple line of a fresh bowel anastomosis should be avoided.

Atrium (Atrium Medical Corporation, Maquet Gentinge Group, Hudson, NH, USA) has developed and manufactures C-Qur™ Film Adhesion Barrier, a novel thin film adhesion barrier for intraperitoneal use in general surgeries. The C-Qur™ Film has been approved for use in humans and received a CE mark on 13 May 2011 (CE number 10123365). The evidence on efficacy and safety of the C-Qur film originates from research on the C-Qur mesh, a mesh with an omega-3 fatty acid coating used for patients with an abdominal ventral hernia. The C-Qur mesh was found to be safe in intraperitoneal use and reduces adhesions to the mesh [14]. The C-Qur™ Film falls into the category of local coverage adhesion barriers. The C-Qur™ Film is an adhesion barrier consisting of a non-adhesive omega-3 fatty acid layer on one side and a Na-CMC (sodium-carboxymethylcellulose) tissue adherent coating on the other side. It is fully resorbable and designed to adhere to the site of treatment for a time that is sufficient to minimize postsurgical adhesion formation and clearance from the site of treatment within approximately 60 days. In contrast to Seprafilm™, The C-Qur™ Film is a one-sided adherent, resulting in good handling characteristics. It offers the potential patient benefits of reduced adhesion formation and corresponding reduction of small bowel obstruction, secondary infertility, pain and adhesiolysis at repeat surgery. The aim of this study is to assess the efficacy and safety of C-Qur™ Film to decrease the incidence of adhesions after colorectal surgery.

## Methods/Design

The CLIPEUS trial is registered with the ClinicalTrials.gov Identifier NCT01872650. The protocol was ethically approved by the official Independent Review Board Nijmegen (2013/470) and registered nationally (NL45940.091.13) [15].

### Design

The CLIPEUS trial is a prospective, investigator-initiated, randomized controlled, double-blinded, multicenter trial. Treatment with the C-Qur™ film adhesion barrier will be compared with no treatment with an adhesion barrier in patients undergoing colorectal surgery with temporary diverting ostomy. The surgeons who have agreed to participate in the study and perform the index procedures will be trained in the placement of C-Qur™ Film and in adhesion mapping.

Patients will be included at the outpatient clinics of the participating centers (Radboud University Medical Center, Nijmegen; Catharina Hospital, Eindhoven; Atrium Medical Center, Heerlen; Maxima Medical Center, Veldhoven; Gelderse Vallei Hospital, Ede) by the treating surgeons. During the operation, when the definite decision to create a temporary ostomy is made, patients are randomized 1:1 to either the treatment arm (C-Qur™ film) or the control arm (standard treatment: no adhesion barrier, no placebo). In patients assigned to the treatment arm, the C-Qur™ Film must be applied beneath the incision. The C-Qur™ film can also be applied to other areas considered to be adhesiogenic (for example, the dissection site and ostomy site, but not around the anastomosis). The number of C-Qur™ Film sheets placed is limited to a maximum area of coverage of 774 cm^2^ (Table 1). Patients will return 8 to 16 weeks post-colorectal resection to have their diverting ostomy taken down. During the takedown, the incidence, extent and severity of the adhesions will be evaluated.

**Table 1 Tab1:** **Maximum area of coverage and number of sheets**

Code	Size (cm)	Maximum	
		Area (cm ^2^)	Number of sheets
32024	7.5 × 10.0	774	10
32025	7.5 × 12.5	774	8
32029	10.0 × 10.0	774	7
32031	12.5 × 15.0	774	4

### Patients

Patients aged 18 years or older who require open or hand-assisted laparoscopic colonic or rectal resection for colorectal disease with the formation of a temporary diverting loop ileostomy or colostomy and a planned closure within 8 to 16 weeks and who visit the outpatient clinic at one of the participating centers will be invited to participate in this trial.

Inclusion criteria are an incision of 6 cm or longer in case of hand-assisted laparoscopy and signed informed consent.

Exclusion criteria include the following: pregnancy, patients for whom it is known prior to the initial procedure that loop ileostomy or colostomy closure between 8 and 16 weeks is not feasible, active intra-abdominal infection such as peritonitis, abdominal abscess, anastomotic leakage or fistula (interloop abscess in the resection specimen is not an exclusion criterion), endometriosis, known allergies to any component of the C-Qur Film device, an additional procedure at the time of loop ileostomy or colostomy takedown deemed interfering with adhesion assessment by the treating surgeon, intended use of intraoperative lavage/irrigation with any anti-adhesion solutions other than lactated ringers and/or saline (for example, dextran, heparin, corticosteroids, icodextrin, any other irrigant that is believed to have anti-adhesion properties) or an adhesion barrier other than C-Qur Film™, (planned) administration of systemic agents with the intention to prevent adhesion formation within 30 days prior to the index procedure, planned chemotherapy and/or abdominal radiotherapy between index surgery and loop ileostomy or colostomy takedown, use of immune system suppressants deemed by the surgeon to interfere with wound healing (patients taking daily doses of corticosteroids exceeding 20 mg within the prior 30 days are to be excluded; patients requiring perioperative corticosteroid supplementation are not to be excluded), impaired immune system function or coagulation disorders deemed by the surgeon to interfere with wound healing, a known history of severe multiple drug allergies, a life expectancy of less than 6 months because of a medical condition or disease state, a medical condition or other serious condition that will interfere with compliance and/or ability to complete this study protocol or patients who in the opinion of the investigator would not be a good candidate for enrolment, or participation in a study of another investigational device or drug.

### Intervention

All patients will undergo a colorectal resection with the creation of a temporary loop ileostomy or loop or split colostomy. During this index operation, adhesions, if any, will be mapped. The incidence, location, extent and severity and any treatment of adhesions will be noted. For quantifying the extent of adhesions to the abdominal wall and between organs, the abdominal wall is divided into nine segments and the abdominal cavity into ten segments (Figure 1). Severity of the adhesions will be classified according to the Zühlke classification (Table 2) [16]. Classification of operative wounds based on degree of microbial contamination, number of serosal injuries and number of inadvertent enterotomies will also be noted in the source notes and CRF (case report form).

**Figure 1 Fig1:**
[figure not shown]
**Segments of the abdominal wall and segments of the abdominal cavity. a**. The nine segments of the abdominal wall; **b**. The ten segments of the abdominal cavity.

**Table 2 Tab2:** **Adhesion classification system according to Zühlke**
[16]

Score	Observation
0	No adhesions
1	Adhesions that are filmy and easy to separate by blunt dissection
2	Adhesions where blunt dissection is possible but sharp dissection necessary, beginning vascularization
3	Lysis of adhesions possible by sharp dissection only, clear vascularization
4	Lysis of adhesions possible by sharp dissection only, organs strongly attached with severe adhesions, damage of organs hardly preventable

For patients randomized to the C-Qur™ Film arm, the C-Qur™ Film must be applied to the viscera underneath the primary or specimen retrieval incision in case of hand-assisted laparoscopy. Preferably, the C-Qur™ Film is also applied to other areas considered to be adhesiogenic, such as the peritoneal dissection planes and the ileum or colon at the ostomy site. The number of C-Qur™ Film sheets placed in the abdomen is limited to a maximum area of coverage of 774 cm^2^. In case sheets of the largest size (15 cm × 12.5 cm) are used, the maximum is four sheets (Table 1). The application of C-Qur™ Film directly to a fresh bowel anastomosis is not allowed.

### Control arm

Patients who are not allocated to the treatment group will receive standard treatment, which means no C-Qur™ Film or any other treatment considered to have anti-adhesion properties (for example, corticosteroids, dextran, heparin, icodextrin, *etcetera*) and no placebo will be used.

### Outcome measures

The primary outcome measure will be the incidence of adhesions to the primary incision site or the specimen retrieval incision in the case of hand-assisted laparoscopy.

Secondary outcome measures on effectiveness are the extent and severity of adhesions to the primary incision site or specimen retrieval incision, incidence, extent and severity of adhesions at the loop ileostomy or loop/split colostomy site and of adhesions at areas potentially injured during the initial procedure, duration of ileostomy or loop/split colostomy takedown from the start of the takedown to the time the bowel is repositioned in the abdomen, percentage (%) of abdominal wall with adhesions, number of C-Qur™ barrier films used, sizes of C-Qur™ barrier films used, areas treated with C-Qur™ Films (underneath incision, ostomy bowel loops, other areas injured during initial procedure and considered adhesiogenic), reason for not placing film in one or more of the areas considered to be adhesiogenic, incidence of chronic abdominopelvic pain, incidence of other gastrointestinal complaints, quality of life as assessed by Short Form-36 and DASI, and total direct health care costs (30 days-in-hospital healthcare costs during both hospital stays).

Secondary outcome measures on safety are incidence of postoperative complications. Complications are divided into surgical and medical complications. Surgical complications are superficial incisional surgical site infections, deep incisional surgical site infections, anastomotic leakage, intra-abdominal abscess, peritonitis, unexplained fever, fascia dehiscence, wound dehiscence, postoperative hemorrhage, and postoperative ileus (POI). Medical complications are pulmonary embolism, pneumonia, urinary tract infection, sepsis, and death.

Other secondary outcome measures are reoperations, number of re-laparotomies, number of inserted central venous lines, other re-operations, first postoperative day of oral food intake, parenteral feeding, number of days parenteral feeding required, tube feeding, number of days tube feeding required, first postoperative day of passing flatus, first postoperative day of passing stool, usage of pain medication, daily VAS (Visual Analog Scale) scores, hospital stay, Intensive Care Unit stay, Recovery Unit stay, readmissions within 30 days after discharge, and in-hospital mortality.

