### Randomization and blinding

Intra-operatively, the treating surgeon judges whether the patient is eligible for definite inclusion. Prior to formation of the temporary loop ileostomy, loop or split colostomy, included patients will be randomized. Patients will be randomized in a 1:1 fashion to the C-Qur™ Film arm (treatment arm) or the control arm. The randomization will be stratified by operative technique (open or hand-assisted laparoscopy). The allocation sequence will be computer-generated through the web-based program Alea©. A researcher who does not participate in the data analysis will manage the randomization process. This way, the researcher who will perform the data analysis is blinded from treatment allocation. Concealment of treatment allocation and blinding of the surgeon performing the index procedure is not possible because the patient will either get the intervention or does not get an intervention at all. Randomization will be noted in the operation reports, allocation will not.

The patient and doctor at the surgical ward who will complete the case report form during the post-operative period is blinded from treatment allocation. To achieve blinding during the data collection of outcome parameters, the surgeon who will perform the ostomy takedown procedure, will not be the same surgeon as the one who performed the index procedure. Because of the absence of clinical notes regarding allocation, however, the initial surgeon is allowed to do the ostomy takedown in case of man-power or organizational problems.

During the postoperative period after the ostomy takedown, the physician at the ward, who will collect the data regarding the post-operative parameters, will be blinded from the treatment allocation of the patient. The patient will stay blinded for the received treatment.

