### Analysis and sample size

It is hypothesized that the use of the C-Qur™ Film underneath the primary incision reduces the incidence of adhesion at the incision by 30%. This hypothesis is based on the supporting documentation for Seprafilm™ (treatment) versus Control (no treatment) with an adhesion rate of 94% in the control group and 64% in the treatment group [18–22]. We estimate a total drop out of 25% in this study, comprising 10% regular drop out and 15% drop out because of anastomotic leakage. A 15% drop out because of anastomotic leakages is chosen because it is the upper limit of the incidence of this complication. Assuming that the C-Qur™ Film group performs similarly to Seprafilm™, a total of 84 patients, (32 + 10 per group (25% drop out)) would be needed in a randomized study, with 80% power and two-sided alpha = 0.05 in order to detect a 30% reduction in incidence of adhesions.

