### Statistics

In general, for continuous variables, the mean, standard deviation, median, IQR, minimum and maximum values will be presented. Groups will be compared using the *t*-test or Mann-Whitney *U* test, as appropriate, based on the distribution of the data. For categorical variables, the frequencies and percentage within each category will be calculated. Groups will be compared using the chi-square or Fisher’s Exact test, as appropriate, based on the expected counts. All available data will be summarized. Demographics, preoperative, perioperative, and postoperative parameters will be reported and compared for both groups. Descriptive statistics will be presented to describe the trial results. Missing data will be evaluated by the investigators, and appropriate action will be undertaken*.* In case of skewed baseline data between groups, results will be corrected for this data.

Our primary analysis will focus on the effectiveness and safety of the C-Qur film between the treatment group and the control group. A chi-square or Fisher’s Exact test will be performed to assess a significant improvement in the incidence, on the Zühlke score of adhesions underneath the incision site, underneath the loop ileostomy or loop/split colostomy site, and for the extent of adhesions underneath the loop ileostomy or loop/split colostomy site as well. The extent of adhesions underneath the incision site and the time needed for takedown of the ileostomy or loop/split colostomy will be compared using a *t*-test. To assess the safety of the C-Qur film the total incidence of postoperative complications will be compared using a *t*-test or a Mann-Whitney *U* test. The mortality and the incidence for each separate complication will be compared using a chi-square or Fisher’s Exact test.

Subgroup analysis will be performed on laparoscopic versus open colorectal resection, and on ileostomy versus colostomy for the incidence, extent and severity of adhesions as described above. Since data collection of the outcome parameters is not blinded when the same surgeon who performed the index procedure also takes down the ostomy, subgroup analysis will be performed for patients with and without blinded data collection of outcome parameters.

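### The general test rule would send skewed total costs to Mann-Whitney, which does not test the difference in mean cost

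*Protocol article*

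**What the plan says.** The Outcome measures section of the protocol article ends its list of secondary effectiveness outcomes with "total direct health care costs (30 days-in-hospital healthcare costs during both hospital stays"). No section gives a method specific to costs.

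The Statistics section opens with a rule that applies in general to continuous variables: "Groups will be compared using the *t*-test or Mann-Whitney *U* test, as appropriate, based on the distribution of the data". It also promises description: "for continuous variables, the mean, standard deviation, median, IQR, minimum and maximum values will be presented". Later it departs from the general rule and fixes a t-test for two outcomes only: "The extent of adhesions underneath the incision site and the time needed for takedown of the ileostomy or loop/split colostomy will be compared using a", with that test named at the end. Costs are not one of them, so they stay under the general rule.

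**The concern.** A statement about total cost is a statement about the arithmetic mean: mean cost per patient times the number of patients gives the bill. Mann-Whitney asks something else, namely whether a patient in one arm tends to rank above a patient in the other.

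The two questions have the same answer in direction when the arms differ only by a shift or a common scale. They can part company when the shapes differ, and here there is a plausible reason for that. The Design and Intervention sections require film in every treated patient, which is a small, uniform addition to cost. Leakage, reoperation and intensive care, all collected in this trial, fall on a minority and make the upper tail. Ranks register the uniform addition and give little weight to how far out the tail lies. The p-value attached to costs could then favour the arm with the higher mean.

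**Working it through.** **The plan's own figures.** The article states no figure for costs. Its sample size concerns the primary outcome: 94% v 64%, "with 80% power and two-sided alpha = 0.05". By exact enumeration with Fisher's test, power is 0.790 at 31 per group and 0.809 at 32, so the stated 32 reproduces. Adding 10 per group gives 42, and 84 in total. The cost point needs only the group size of 42.

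**Assumed inputs (none is in the article).**
- Base cost per patient: log-normal, median 10,000, log-SD 0.25, 0.5 or 0.75, same in both arms.
- Complication add-on A: log-normal, median 30,000, log-SD 0.4.
- Complication rate: 20% control; 15% or 12% film.
- Film cost, added to every treated patient: 500 to 1,500.

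**True mean difference (film minus control).** The base cost cancels.
- E[A] = 30,000 × exp(0.4²/2) = 30,000 × exp(0.08) ≈ 32,499.
- Difference = film cost − (control rate − film rate) × 32,499.
- 20% v 15%, film 1,500: 1,500 − 0.05 × 32,499 ≈ −125.
- 20% v 12%, film 1,500: 1,500 − 0.08 × 32,499 ≈ −1,100.

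**Would the rule pick Mann-Whitney?** With base log-SD 0.25, a Shapiro-Wilk test rejects normality in at least 99.6% of simulated control arms, at 32 and at 42 per group.

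**How often Mann-Whitney is significant with the film arm costlier** (42 per group, two-sided 5%, 2,000 to 4,000 simulated trials per setting):

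| Base log-SD | Film cost | 20% v 15%: true difference | Declared costlier | 20% v 12%: true difference | Declared costlier |
|---|---|---|---|---|---|
| 0.25 | 1,500 | −125 | 29–30% | −1,100 | 22–24% |
| 0.25 | 750 | −875 | 8.1% | −1,850 | 5.1% |
| 0.25 | 500 | −1,125 | 4.4% | −2,100 | 2.5% |
| 0.5 | 1,500 | −125 | 9.0% | −1,100 | 6.3% |
| 0.75 | 1,500 | −125 | 5.0% | −1,100 | 3.5% |

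At log-SD 0.25, a film cost of 1,000 gives 9.4% for 20% v 12%. With the wider spread and the cheaper film together, the figure falls to about 1%. At 32 per group the top row becomes 23.5% and 19.0%. For reference, identical arms would give 2.5% in this direction, so cells near or below that show no problem.

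**The mean comparison in the top row.** For 20% v 15%, the Welch t-test is significant in either direction in 5.1% of trials. For 20% v 12%, it calls film costlier in 1.0%.

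**A control case.** With log-SD 0.8 in both arms and equal means, Mann-Whitney rejects in about 5% of trials, as it should. Skew alone does not cause the conflict; a difference in shape does.

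**Precision of the mean difference** (20% v 12%, log-SD 0.25).
- E[A²] = 32,499² × exp(0.16) ≈ 1.239 × 10⁹.
- Base variance = (10,000 × exp(0.03125))² × (exp(0.0625) − 1) ≈ 6.87 × 10⁶.
- Arm variance = p × E[A²] − (p × E[A])² + base variance, so the SD is about 14,577 (control) and 11,848 (film).
- Standard error = √((14,577² + 11,848²)/42) ≈ 2,899; 95% half-width = 1.96 × 2,899 ≈ 5,680, against a true difference of −1,100.

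**The case against.** The strongest reply is that the article commits to nothing for costs. The rule is introduced as general, the test is to be chosen as appropriate, and costs are never named in the Statistics section. A condensed article may fairly leave cost methods to a fuller protocol or analysis plan. A reader might infer that the plan prescribes Mann-Whitney for costs; the text does not support that. What stands is narrower: the article does state a rule, costs fall within its scope, and no exception is made for them although two other outcomes get one. The point is about that stated rule, not about missing detail.

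The second reply is that arm means and SDs will be shown, so a reader could see the means pointing against the rank test and work out an approximate interval. This stands and limits the harm. But under the rule the reported p-value would not test the mean difference.

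The third reply is that the size depends on invented inputs. This stands too. A reader might infer from the top row that a wrong-direction cost result is a one-in-four risk. The article gives no film price, stay cost or complication cost to support that, and the figure drops to single digits once the base spread is wider or the film costs 750 or less.

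Finally, neither method would settle the cost question in 84 patients: in the 20% v 12% top-row setting the Welch test favours film in only about 5% of trials. That is true, but a wide interval on the right quantity is still more useful than a p-value on a different one.

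**Conclusion.** The point holds as a cheap improvement. As written, the general rule would probably take total costs to Mann-Whitney, which does not test the difference in arithmetic mean cost and can disagree with it in direction. Under the assumed inputs, it declares the film arm costlier in about 1% to 30% of trials although the film arm's true mean cost is about equal or lower. The high end requires a narrow base spread (log-SD 0.25) and a film cost of 15% of the median stay (1,500/10,000).

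The conclusion rests on costs being skewed and on the arms differing in shape rather than only in level. The size of the tail also depends on whether patients counted as drop-outs for anastomotic leakage in the Analysis and sample size section stay in the cost comparison. Costs are a secondary outcome, and nothing here touches the primary analysis. A reader might go further and infer that the trial's cost conclusion will have the wrong sign; the documents support only that it could, if the p-value were read alone.

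**What to change.** Add one sentence to the Statistics section that exempts costs from the distribution rule: report the difference in arithmetic mean total cost per randomised patient with a bootstrap 95% confidence interval (bias-corrected, for example), and give medians and IQR as description only.

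The cost is that sentence and a short bootstrap program. Sample size, data collection and conduct do not change, and the Trial status section says that inclusion has not begun, so the change can be made before any data exist. The downside is that the interval will be wide with 84 patients, which shows fairly how little the trial can say about cost.
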